## Abstract

**Background:**

Many patients develop chronic postsurgical pain (CPSP) after cardiac surgery, which interferes with their sleep, mood, and quality of life. Studies have suggested that propofol improves postoperative analgesia compared with volatile anesthetics, but its preventive effect on CPSP following cardiac surgery is still unknown. This study compares the incidence of CPSP following cardiac surgery for those receiving volatile anesthesia and those receiving propofol-based total intravenous anesthesia (TIVA) using criteria recommended by the Initiative on Methods, Measurement, and Pain Assessment in Clinical Trials (IMMPACT).

**Methods/design:**

This is a prospective randomized controlled trial. In total, 500 adults undergoing cardiac surgery will be randomly allocated to the volatile or the TIVA group. The volatile group will receive sevoflurane or desflurane during surgery as general anesthesia. The TIVA group will receive propofol-based intravenous agents and no volatile agents during surgery. The primary outcomes will be the frequency of CPSP at 3 months, 6 months, and 1 year after surgery. In this case, CPSP is sternal or thoracic pain. It is defined as either (1) numerical rating scale (NRS) > 0 or (2) meeting all six IMMPACT criteria for CPSP. The IMMPACT criteria are validated pain instruments.

**Discussion:**

To our knowledge, this is the first prospective randomized controlled trial to investigate the prevention of CPSP following cardiac surgery for patients receiving volatile anesthesia compared to those receiving propofol-based TIVA using validated pain instruments in accordance with the IMMPACT recommendations. This study will provide important information on which of these two anesthetic regimens is better for preventing CPSP after cardiac surgery.

**Trial registration:**

Chictr.org.cn, ChiCTR1900020747. Registered on 16 January 2019.

## Background

Cardiac surgery is one of the most common forms of major surgery, with over 2 million patients undergoing this procedure worldwide each year [1]. Many patients develop chronic postsurgical pain (CPSP), which can occur in the anterior thorax after a median sternotomy [1]. It is estimated that CPSP has an incidence of 11–56% in patients undergoing cardiac or thoracic surgery, depending on the study population and length of follow-up [2–5]. CPSP that persists after cardiac surgery is a major clinical problem, because it disturbs daily life and interferes with sleep, mood, and quality of life [6–8]. Considering the large number of patients who undergo cardiac surgery, identifying potential treatments for CPSP is important [9]. In addition to standard postoperative analgesics, it has been suggested that corticosteroids, N-methyl-D-aspartate (NMDA) antagonists, alpha-2 agonists, local anesthetics, and gabapentinoids can reduce the risk of CPSP after cardiac surgery [5]. However, no specific therapy has been demonstrated to protect against CPSP [10–12].

Patients undergoing cardiac surgery need general anesthesia from either intravenous (IV) anesthetics (such as propofol) or volatile anesthetics (such as isoflurane, sevoflurane, and desflurane). Studies have found that propofol has anti-inflammatory and antioxidative effects on the biosynthesis of cytokines, which are important in pain signaling [13]. Propofol’s ability to scavenge free radicals is useful and important. It has antioxidant properties and may also dynamically protect the body [14]. Moreover, propofol can modulate NMDA receptors in neurons in vivo, which play a crucial role in the transmission and maintenance of the pain signaling pathway [14, 15]. These anti-inflammatory, free radical scavenging, and NMDA receptor antagonistic properties of propofol imply that it may have a possible perioperative analgesic effect. The meta-analyses by Qiu et al. and Peng et al. suggest that propofol improved postoperative analgesia compared with inhalational anesthesia [16, 17]. However, most previous studies were not designed to detect differences in chronic pain [16, 17], and a few clinical trials investigating CPSP focused on non-cardiac surgery [18, 19]. To date, no published clinical trial has compared the effects of volatile anesthesia with those of propofol-based total intravenous anesthesia (TIVA) in preventing CPSP after cardiac surgery through sternotomy.

Prior studies focusing on CPSP after either cardiac or non-cardiac surgery assessed pain using a yes or no scoring system or a numerical rating scale (NRS) to evaluate the level of pain. Few studies have used the Initiative on Methods, Measurement, and Pain Assessment in Clinical Trials (IMMPACT) recommendations to evaluate CPSP [20]. The IMMPACT approach to assessing CPSP evaluates the quality of the pain, the degree of pain at rest and during movement, the clinical meaningfulness of the pain, and the influence of pain on physical and emotional functioning, instead of focusing on only the absence or presence of pain [20–23]. Thus, the aim of this randomized controlled trial is to assess the prevention of CPSP following cardiac surgery through sternotomy for patients receiving volatile anesthesia compared to those receiving propofol-based TIVA using validated pain instruments in accordance with the IMMPACT recommendations.

## Methods/design

### Study design, approval, and registration

The planned study is a parallel-group randomized controlled trial with a 1:1 allocation ratio undertaken in West China Hospital of Sichuan University. Figure 1 is the trial flowchart. Recruitment commenced in February 2019. Additional file 1 is the Standard Protocol Items: Recommendations for Interventional Trials (SPIRIT) checklist. The schedule of enrollment, interventions, and assessments follows the SPIRIT Figure (Additional file 2). The study has been approved by the ethics committee of West China Hospital of Sichuan University and has been prospectively registered at Chictr.org.cn (ChiCTR1900020747).

**Fig. 1 Fig1:**
[figure not shown]
Consort diagram of study participant flow. TIVA total intravenous anesthesia, NRS numeric rating scale, IMMPACT Initiative on Methods, Measurement, and Pain Assessment in Clinical Trials, QoR-15 15-item Quality of Recovery Questionnaire

### Study aim

The aim of our study is to compare the incidence of CPSP following cardiac surgery for patients receiving volatile anesthesia and those receiving propofol-based TIVA using the IMMPACT criteria.

### Participants

We plan to enroll 500 participants aged more than 18 years undergoing a cardiopulmonary bypass (CPB) for any elective cardiac surgical procedure via a median sternotomy such as procedures that involve the valves, coronary arteries, or aorta, or combined procedures.

#### Inclusion criteria

Participants must meet all the inclusion criteria:
Aged older than 18 yearsUndergoing a CPB for cardiac surgery via a median sternotomySigned the informed consent form

#### Exclusion criteria

Patients who meet any of the following criteria will be excluded from participation:
Those undergoing combined cardiac and non-cardiac surgeryThose undergoing emergency surgeryPregnant womenThose with a suspected family history of malignant hyperthermia or propofol infusion syndromeThose who fail to cooperate with the follow-up procedures due to a lack of understanding of the study procedures

### Randomization, allocation, and concealment

Once informed consent has been received and the preoperative assessments completed, patients will be entered into the trial. Subjects will be allocated using a web-based centralized dynamic randomization service. The dynamic randomization considers patient characteristics including age, gender, European System for Cardiac Operative Risk Evaluation (EuroSCORE) score, predicted CPB duration, and body mass index. The anesthesiologists will be aware of patients’ group allocation because they will provide the trial intervention, but they will not be involved in either the postoperative treatment or the analysis. Patients, intensive care physicians, data collectors, and outcome adjudicators are blinded to treatment allocation.

### Interventions

Patients who meet the enrollment criteria will be randomized 1:1 to either the volatile or the TIVA group. Three investigators ([name], [name], and [name]) will explain the treatment intervention in detail and supervise the compliance of the intervention throughout the entire procedure (from maintenance of anesthesia to transport to an intensive care unit).

#### The volatile group

The volatile group will receive sevoflurane or desflurane to provide general anesthesia during surgery from maintenance of anesthesia to transport to an intensive care unit, including during CPB. Maintenance of anesthesia in the treatment group uses sevoflurane or desflurane at a minimum end-tidal concentration of 0.5–2 minimal alveolar concentration throughout the entire procedure. During CPB, patients will receive sevoflurane or desflurane from a vaporizer connected to an air blender, which is connected to an oxygenator. The minimal alveolar concentration is measured at the outlet of the oxygenator of the extracorporeal circulation.

#### The TIVA group

The TIVA group will receive propofol at an infusion rate of 3–8 mg kg^− 1^ h^− 1^ with or without other IV agents. The only absolute criterion for this group is that no volatile anesthetic is to be used at any time during the procedure.

### Perioperative management

#### Induction of anesthesia

General anesthesia will be induced with midazolam, sufentanil, and propofol as necessary. Tracheal intubation will be facilitated with either rocuronium or cisatracurium. There is no restriction on the type or dose of anesthetic used to induce anesthesia.

#### Ventilation

Patients will be ventilated using a lung-protecting ventilation strategy before and after CPB. The pressure-controlled ventilation will maintain a tidal volume of 6–8 ml kg^− 1^ based on ideal body weight, a positive end expiratory pressure of 5–8 cm H_2_O, an inspiratory to expiratory ratio of 1:2; an inspired oxygen fraction of 0.4 to 0.8, and a respiratory rate of 10–16 per min adjusted to keep a desired end-tidal CO_2_ of 35–45 mmHg. A recruitment maneuver with a peak airway pressure of 30 cmH_2_O for 30 s, as an essential part of the protective ventilation strategy, will be performed before beginning and before discontinuing CPB and exiting from the operating room. The use of ventilation during CPB will be chosen by the anesthesia care providers.

#### Anesthesia maintenance

Propofol or inhalation anesthetics plus sufentanil and a nondepolarizing muscle relaxant will be used to maintain general anesthesia with dosages at the discretion of the attending clinicians. Sufentanil will be administered to avoid changes of mean arterial pressure of more than 20% from baseline while maintaining a mean arterial pressure of at least 65 mmHg. A vasopressor will be administered as necessary. Remifentanil will be administered at an infusion rate of 0.1–0.2 μg kg^− 1^ min^− 1^. The dosage of dexmedetomidine will be limited to less than 0.5 μg kg^− 1^ h^− 1^ if needed. No antiemetics will be administrated for nausea or vomiting prophylaxis.

#### Postoperative analgesia

After surgery, patients will be transferred to an intensive care unit for further care. Patients will receive an infusion of 10–25 μg kg^− 1^ h^− 1^ morphine or 100 mg of IV meperidine to maintain an NRS of less than 4 (0 = no pain, 10 = worst pain imaginable), as assessed by the nursing personnel. IV analgesia will be discontinued, and patients will be given oral celecoxib or ibuprofen when they can tolerate oral medication. Patient-controlled IV analgesia pumps will not be used.

### Data collection

#### Baseline characteristics of patients

Demographic data, cardiac history, coexisting medical conditions, comorbidities, smoking status, EuroSCORE score, depression and anxiety history, chronic pain at presentation in an area other than the operative site, surgical procedure, intraoperative sufentanil and remifentanil dosage, and health-related quality of life measured with the 15-item Quality of Recovery Questionnaire (QoR-15) [24] will be recorded.

#### Acute pain assessment at 24, 48, and 72 h after surgery

Patients will be visited and evaluated over the first 72 h after surgery. Pain is assessed using an 11-point NRS scale (0 = no pain, 10 = worst pain imaginable) at 24, 48, and 72 h after surgery. The amount of opioid analgesics consumed is determined from their electronic medical record and is converted to an equivalent dose of IV morphine [25].

#### Follow-ups at 3 months, 6 months, and 1 year

Each patient will receive follow-up phone calls at 3 months, 6 months, and 1 year after surgery to answer questions regarding the presence, quality, and severity of pain using the Brief Pain Inventory [26], the McGill Short Form Questionnaire [27], and the QoR-15 questionnaire [24]. Each patient will leave at least three phone numbers and receive a maximum of three telephone calls if contact could not be made.

### Outcomes

#### Primary outcome

The primary outcome is the occurrence of CPSP at 3 months, 6 months, and 1 year after surgery. CPSP is defined as sternal or thoracic pain that the patient identifies as related to their surgery in two ways: (1) NRS > 0 and (2) pain that meets all six IMMPACT criteria for CPSP. The IMMPACT criteria are validated instruments for assessing pain [28].

#### IMMPACT Questionnaires

Chronic pain is assessed in accordance with the IMMPACT recommendations in the following six domains [28]: (1) absence or presence of pain in the area of surgery, (2) clinically important daily average pain (NRS ≥ 4 on a 0- to 10-point scale), (3) clinically important pain at rest (NRS ≥ 4), (4) clinically important pain intensity upon movement or activity (NRS ≥ 4), (5) quality of pain, and (6) physical and emotional functioning [21, 22, 29]. The Brief Pain Inventory is used to determine the domains 1 to 4 and 6. It measures the intensity of daily average pain, pain at rest, pain during movement or activity, as well as physical and emotional functioning [26]. The McGill Pain Questionnaire is used to assess domain 5, which relates to the impact of both sensory and affective pain [27]. A total pain index score ≥12 is associated with chronic pain [30]. Subjects have to meet the threshold for all six outcome domains to fulfill the IMMPACT criteria.

#### Secondary outcomes

The secondary outcomes are: (1) NRS pain scores (0–10) 24, 48, and 72 h after surgery, (2) opioid consumption during the first 72 h after surgery, (3) the Brief Pain Inventory, the McGill Pain Questionnaire, and health-related quality of life measured with QoR-15 at 3 months, 6 months, and 1 year after surgery.

### Statistics

#### Sample size estimate

The sample selected for this study was based on the finding of our prior study exploring the incidence and possible risk factors of CPSP in patients undergoing cardiac surgery with CPB via a median sternotomy. That study showed that 60.9% patients had CPSP at 3 months postoperatively [31]. The sample size for the current study is 250 patients per group, for a total of 500 patients. The study has 80–90% power to detect a 25 relative risk reduction for the primary outcome of CPSP at 3 months at a significance level (alpha) of 0.05 (two-sided), anticipating a 50–60% CPSP rate in the control (inhalation or TIVA) arm with an allowance of 10% of patients lost to follow-up, or withdrawn or withdrawing from the study.

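### With the stated 10% loss, power at the 50% control rate is about 76%, not 80%; the stated lower end holds only if nobody is lost

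*Protocol article*

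**What the plan says.** All of this is in the protocol article. The section Sample size estimate fixes the number: "The sample size for the current study is 250 patients per group, for a total of 500 patients". The power claim is "The study has 80–90% power to detect a 25 relative risk reduction for the primary outcome of CPSP at 3 months", at a two-sided alpha of 0.05, "anticipating a 50–60% CPSP rate in the control (inhalation or TIVA) arm", and "with an allowance of 10% of patients lost to follow-up, or withdrawn or withdrawing from the study". The empirical starting point is the group's own earlier study: "That study showed that 60.9% patients had CPSP at 3 months postoperatively".

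The section Participants shows what the 500 counts: "We plan to enroll 500 participants aged more than 18 years". Participant timeline likewise reports 500 patients enrolled by the end of June 2019. So 250 per group is the number before losses. Statistical analyses names the chi-squared or Fisher's exact test for the primary outcome.

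**The concern.** The power range is presented as already allowing for 10% loss. If so, the lower figure of 80% should come from 225 patients per arm at the lower control rate of 50%. It does not. It comes out only when all 250 per arm are analysed.

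Power for CPSP at 3 months is the only justification given for the sample size. If the control rate turns out near 50%, the trial's planned chance of missing a 25% relative reduction is about 24%, not 20%. A reader who relies on the stated range would credit the design with more sensitivity than it has at the less favourable end of its own assumptions.

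**Working it through.** **Inputs.** From Sample size estimate: 250 per group, two-sided alpha 0.05, control rate p₁ of 50% to 60%, relative reduction of 25, loss 10%. From Study design, approval, and registration: 1:1 allocation. The percent sign is missing after the 25. I read it as 25%, so p₂ = 0.75 × p₁, which is 37.5% at the lower end and 45% at the upper end.

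**Analysable patients.** 250 × (1 − 0.10) = 225 per arm.

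**Formula.** Normal approximation to the uncorrected chi-squared test, with p̄ = (p₁ + p₂)/2:

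- SE₀ = √[2 p̄(1 − p̄)/n]
- SE₁ = √[(p₁(1 − p₁) + p₂(1 − p₂))/n]
- power = Φ[(p₁ − p₂ − 1.96 × SE₀)/SE₁]

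**Reproducing the stated 80%: no loss, n = 250, 50% versus 37.5%.** p̄ = 0.4375, SE₀ = 0.0444, SE₁ = 0.0440. The argument of Φ is (0.125 − 0.0870)/0.0440 = 0.864, so power = 80.6%.

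**With the 10% loss: n = 225, 50% versus 37.5%.** SE₀ = 0.0468, SE₁ = 0.0464. The argument is (0.125 − 0.0917)/0.0464 = 0.718, so power = 76.4%.

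**Across the range of control rates:**

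| Control rate | Other arm | n = 250 (no loss) | n = 225 (10% loss) |
|---|---|---|---|
| 50% | 37.5% | 80.6% | 76.4% |
| 55% | 41.25% | 87.0% | 83.4% |
| 60% | 45% | 92.1% | 89.3% |
| 60.9% (prior study) | 45.7% | 92.9% | 90.2% |

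**Does the choice of method matter?** At 50% versus 37.5% with n = 225:

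- unpooled variance: 76.9%
- arcsine: 76.4%
- log relative risk: 75.3%
- exact enumeration of the Pearson test: 76.8%
- exact enumeration of the continuity-corrected test: 73.8%

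No two-sided method reaches 78%. The milder loss convention, 250/1.1 or about 227 per arm, gives 76.7% (exact 77.4%). A one-sided 0.05 test would give 85.0%, but the text says two-sided.

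**Sample size for 80% at the 50% rate.** n = [1.96 √(2 × 0.4375 × 0.5625) + 0.8416 √(0.25 + 0.2344)]² / 0.125² = (1.3750 + 0.5857)² / 0.015625 = 246.1, so 247 analysable per arm. Allowing for 10% loss, 246.1/0.9 = 273.4, about 274 enrolled per arm (275 if 247 is inflated instead).

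**What 225 per arm does deliver.** 80% power for a 25% reduction is reached from a control rate of about 52.5%. At a 50% control rate, 80% power holds for a relative reduction of 26.1% (50% versus 36.9%).

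**The case against.** The strongest case is that this is a rounded range and the error sits in one corner of it. With the loss applied, power is 83.4% at a 55% control rate, 89.3% at 60% and 90.2% at the prior-study rate on which the sample size is said to be based. Only the lowest quarter of the 50–60% band falls short, by less than 4 points. That stands, and it sets the size of the finding. It does not rescue the lower bound: the authors chose 50% as the lower end and attached the 10% allowance to the same sentence.

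Intention-to-treat analysis might be said to keep 250 per arm. Only in part. CPSP is collected by telephone with at most three calls, so a patient who is never reached has no observed outcome. The article describes no imputation, an unseen analysis plan may do so, and imputation would not be expected to restore the lost information in full.

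The reason for the discrepancy cannot be proved. The lower stated figure fits a no-loss calculation and the upper one fits a calculation with loss; no single calculation gives both closely. A loss adjustment left out at one end and loose rounding are both possible.

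Finally, the interpretation of a null result should rest on the relative risk and its 95% confidence interval, which Statistical analyses promises, and not on planned power. That is right and limits the consequence. The stated power is still a claim about the design that its own inputs do not support.

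**Conclusion.** The concern holds. On the protocol's own inputs the power range is about 76–89%, not 80–90%. The upper end agrees with the text to within a point; the lower end is overstated by 3.6 points (80 − 76.4), and type II error there is about 24% instead of 20%. The conclusion assumes that the 25 means 25% and that patients lost or withdrawn contribute no 3-month outcome. It does not depend on which standard two-sided method is used. No estimate, interval or P value changes, and power at the prior-study rate is not in doubt.

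**What to change.** Correct the power sentence in Sample size estimate, for instance:

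> With 225 evaluable patients per arm (250 randomised, 10% loss), the study has about 76% power at a 50% control rate and 89% at 60% to detect a 25% relative reduction in CPSP at 3 months (two-sided alpha 0.05).

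It would help to add that 80% power is reached from a control rate of about 52.5%, or, at a 50% control rate, for a relative reduction of about 26%. The missing percent sign should be restored at the same time.

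Enrolment of 500 is reported as complete, so no further recruitment is proposed. The cost is one sentence and a slightly less favourable figure; conduct and analysis are unaffected.

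### The 80–90% power claim does not say which of the two primary CPSP definitions it covers, and it does not realistically extend to the six-domain IMMPACT definition named in the study aim

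*Protocol article*

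**What the plan says.** - **Power** (Sample size estimate): "The study has 80–90% power to detect a 25 relative risk reduction for the primary outcome of CPSP at 3 months", with 250 patients per group, two-sided alpha 0.05 and a 10% allowance for loss or withdrawal.
- **Planning rate** (same section): a single range, "anticipating a 50–60% CPSP rate in the control (inhalation or TIVA) arm". Its source is the group's earlier cohort: "That study showed that 60.9% patients had CPSP at 3 months postoperatively". The CPSP definition used in that cohort is not stated.
- **Primary outcome:** surgery-related sternal or thoracic pain, defined in two ways: NRS above 0, and pain meeting all six IMMPACT criteria. The abstract instead joins the two with either/or.
- **IMMPACT rule** (IMMPACT Questionnaires): "Subjects have to meet the threshold for all six outcome domains to fulfill the IMMPACT criteria". Three of the six domains need NRS ≥ 4 (average pain, pain at rest, pain on movement).
- **Study aim:** to compare CPSP incidence between patients on volatile anesthesia and "those receiving propofol-based TIVA using the IMMPACT criteria".
- **Background:** earlier CPSP studies "assessed pain using a yes or no scoring system or a numerical rating scale (NRS) to evaluate the level of pain", and few used IMMPACT.

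No event rate, effect size or power is given for the IMMPACT definition.

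**The concern.** One event rate and one power figure stand for a primary outcome that has two definitions of very different strictness. A patient who meets all six domains has average pain of at least 4 and so also has NRS > 0; the reverse need not hold. The IMMPACT rate can therefore equal the NRS > 0 rate only if every patient with any pain clears all six thresholds. For a fixed relative reduction, power falls as the control rate falls, so a figure derived at 50–60% does not carry over to a rarer event.

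At stake is how the IMMPACT comparison will be read. It is the stated aim and the claimed novelty of the trial. If it is non-significant, the protocol as written attaches an 80–90% power label to that result without a calculation behind it.

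**Working it through.** **Inputs from the protocol.** 250 per group; 10% loss, so 250 × 0.90 = 225 evaluable per arm; 1:1 allocation; two-sided alpha 0.05; control rate 50–60%; "a 25 relative risk reduction", read as 25% relative. The percent sign is missing, but an absolute drop of 25 points would give over 99.9% power, so only the relative reading fits the claim.

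**Input not in the protocol (assumption).** The control rate for six-domain IMMPACT CPSP, varied from 5% to 40%.

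**Formula.** Two-proportion test with n per arm, p2 = 0.75 × p1 and p̄ = (p1 + p2)/2:

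power = Φ{ [ (p1 − p2) − 1.96 × √(2p̄(1 − p̄)/n) ] / √([p1(1 − p1) + p2(1 − p2)]/n) }

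**Step 1: the plan's own figure.**
- p1 = 0.50, p2 = 0.375, n = 225: (0.125 − 1.96 × 0.04677)/0.04640 = 0.718, so power is 76.4%.
- p1 = 0.60, p2 = 0.45, n = 225: (0.150 − 1.96 × 0.04708)/0.04655 = 1.240, so power is 89.3%.
- Exact enumeration of the uncorrected chi-squared test gives 76.8% and 89.7%.
- With all 250 per arm evaluable, the figures are 80.6% and 92.1%.

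The upper end of 80–90% reproduces with the stated loss. The lower end reaches 80% only if the loss is ignored; at a 50% rate, 80% power would need 247 evaluable, or 275 randomized, per arm. The sample size of 250 itself reproduces from 60.9%, 90% power and 10% loss (224 evaluable, 249 randomized per arm).

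**Step 2: the rate at which power reaches 80%.** Solving the formula for p1 with n = 225 gives about 52.5%. Below that control rate, power for a 25% relative reduction is under 80%, whichever definition is used.

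**Step 3: the IMMPACT definition at assumed rates, n = 225.** Worked example at 10%: p2 = 0.075, (0.025 − 1.96 × 0.02664)/0.02661 = −1.02, so power is 15.3%.

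| Assumed IMMPACT control rate | Power for a 25% relative reduction | Relative reduction detectable with 80% power |
|---|---|---|
| 5% | 9.5% | about 87% |
| 10% | 15.3% | about 66% |
| 20% | 28.6% | about 47% |
| 30% | 43.9% | about 38% |
| 40% | 60.5% | about 31% |

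**Step 4: a check tied to the plan's own rates.** Suppose 50–60% is the NRS > 0 rate.
- At 50%, power for IMMPACT cannot exceed 76.4%, even if every patient with pain met all six domains.
- At 60%, 52.5/60 = 87.5% of patients with any pain would have to meet all six domains for 80% power.
- If half did, the IMMPACT rate would be 25–30% and power 36–44%.

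**The case against.** Four points on the other side deserve weight.

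1. **The IMMPACT rate is unknown.** A reader might infer that the IMMPACT comparison has only 10–30% power. The protocol does not support that as a fact: it needs an assumed rate of roughly 5.5–21%, and at 30% or 40% power is 44% or 61%. This objection stands, so only the range and the 52.5% threshold should be reported.
2. **The 50–60% has not been shown to be impossible for IMMPACT.** The definition behind the 60.9% is not given, so a lower IMMPACT rate is a strong inference, not a proof. The Background range of 11–56% does not settle it: it is attributed to population and length of follow-up, and its top lies inside the planning range. This also stands.
3. **The abstract allows a single composite.** Under either/or, the outcome reduces to NRS > 0 and the power statement may well apply to it. But IMMPACT then adds nothing to the primary outcome, and the aim has no powered analysis. The Primary outcome section reads more naturally as two definitions. The text needs clarifying under either reading.
4. **Imprecision will be visible.** The Statistical analyses section plans relative risks with 95% confidence intervals, and nowhere does the protocol say that a null result would be taken as no effect. This softens the consequence but does not correct the power statement.

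**Conclusion.** The concern holds as a defect in the power statement. The protocol claims 80–90% power for a primary outcome with two definitions, from one rate of unstated definition. That claim does not extend to the six-domain IMMPACT definition unless its control rate is at least about 52.5%, which is unrealistic for a subset of any pain planned at 50–60%. How far power falls short cannot be fixed from the protocol: about 10% to 61% across assumed rates of 5% to 40%, given 225 evaluable per arm and the same 25% relative reduction in IMMPACT pain as in any pain. Separately, the lower end of the stated range is slightly optimistic: about 76%, not 80%, once the 10% loss is applied.

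A reader might also infer that IMMPACT must be removed from the primary outcome. That does not follow, because naming the definition covered and reporting the detectable effect would close the gap.

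**What to change.** In the Sample size estimate section:
- say which definition the 60.9%, the 50–60% and the power refer to;
- restate the power as about 76–89% for a 25% relative reduction at 50–60% after 10% loss;
- add a range of IMMPACT control rates, labelled as assumptions, with power or detectable reduction as tabulated above;
- say that a non-significant IMMPACT result is not evidence of no effect.

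Reconcile the abstract, the Study aim and the Primary outcome section on whether the outcome is one composite or two definitions.

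Moving IMMPACT to secondary is optional. The Participant timeline section reports that all 500 patients were enrolled by the end of June 2019, so such a move would change a primary outcome after enrollment. It would have to be documented as a change made before any unblinded comparison.

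The cost is a less favorable power statement and some rewording. No more patients are needed.
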